# Delirium and neuropsychological recovery among emergency general surgery survivors (DANE): study protocol for a randomized controlled trial and collaborative care intervention

**DOI:** 10.1186/s13063-023-07670-w

**Published:** 2023-10-03

**Keywords:** Postoperative delirium, Emergency general surgery

## Abstract

**Background:**

Delirium is a complex neuropsychiatric syndrome which consists of acute and varying changes in cognition and consciousness. Patients who develop delirium are at increased risk for a constellation of physical, cognitive, and psychological disabilities long after the delirium has ended. Collaborative care models integrating primary and specialty care in order to address patients with complex biopsychosocial needs have been demonstrated to improve outcomes in patients with chronic diseases. The purpose of this study is to evaluate the ability of a collaborative care model on the neuropsychologic recovery of delirium survivors following emergency surgery.

**Methods:**

This protocol describes a multicenter (eight hospitals in three states) randomized controlled trial in which 528 patients who develop delirium following emergency surgery will be randomized to either a collaborative care model or usual care. The efficacy of the collaborative care model on cognitive, physical, and psychological recovery in these delirium survivors will then be evaluated over 18 months.

**Discussion:**

This will be among the first randomized clinical trials in postoperative delirium survivors evaluating an intervention designed to mitigate the downstream effects of delirium and improve the neuropsychologic recovery after surgery. We hope that the results of this study will add to and inform strategies to improve postoperative recovery in this patient group.

**Trial registration:**

ClinicalTrials.gov NCT05373017. Registered on May 12, 2022.

## Background

Delirium is a neuropsychiatric syndrome which is characterized by acute and fluctuating changes in cognition and consciousness [1]. It is a devastating, common complication which affects more than one-quarter of patients following emergency surgery. With over 1.5 million emergent and urgent surgeries occurring each year along with an increasing population of older people, delirium and the subsequent neurocognitive decline following surgery are serious public health problems.

Postoperative delirium is also associated with a constellation of adverse downstream effects, which includes increased healthcare resource utilization, lower quality of life, loss of functional independence, and increased risk of Alzheimer’s disease and related dementias (ADRD) [1, 2]. These patients often have complex, cognitive, physical, and psychological morbidity and increased care burden, which may include visits to several healthcare providers and allied health professionals (e.g., physical therapy, speech therapy) and in-home care services. These patients are at particular risk of worse outcomes during care transitions due to fragmentation of care. Care fragmentation in this group is associated with a high risk of readmission, falls, drug overprescribing, poor quality of life, and further decline in function.

The National Academy of Science, Engineering, and Medicine (NASEM) emphasizes that care after acute care hospitalization should be evidence-based, patient-centered, continuous, and without fragmentation. The academy suggests that collaborative care models are a key way to achieve a rapid and full recovery in patient populations that are vulnerable to breakdowns in the coordination of post-acute care [3]. Several randomized controlled trials demonstrate that collaborative care models enhanced quality of life, reduced care fragmentation, and improved psychological morbidity among complex patient populations [4–9]. However, there is no effective, personalized, and scalable care model to manage the morbidity of emergency or unplanned postoperative delirium survivors. Building on our experience designing collaborative care interventions for vulnerable patient populations, we designed a novel collaborative care model that leverages telehealth to target older delirium survivors after emergency surgery. The proposed randomized controlled trial will evaluate the feasibility and superiority of this collaborative care model on the cognitive, physical, and psychological recovery of delirium survivors following emergency surgery when compared to usual care.

## Methods and design

### Study population (Tables 1 and 2)

**Table 1 Tab1:** Study timeline

	Year 1				Year 2				Year 3				Year 4				Year 5			
	1	2	3	4	1	2	3	4	1	2	3	4	1	2	3	4	1	2	3	4
Start-up (hire/train staff, make study manuals, create data entry system)	X	X																		
Enrollment and randomization		X	X	X	X	X	X	X	X	X	X									
Deliver interventions			X	X	X	X	X	X	X	X	X	X	X	X	X					
Outcome measures			X	X	X	X	X	X	X	X	X	X	X	X	X	X	X	X	X	
Data entry and management			X	X	X	X	X	X	X	X	X	X	X	X	X	X	X	X	X	
Analyze data and submit report to DSMB				X	X	X	X	X	X	X	X	X	X	X	X	X	X	X	X	X
Present results at national meetings																		X	X	X

**Table 2 Tab2:** Schedule of activities

	Screening, day 14–0	Enrollment/baseline, day 0	Acute stage, months 0–1	Recovery state, months 2–6	6-month follow-up, weeks 21–31	Maintenance stage, months 7–12	12-month follow-up, weeks 47–57	18-month follow-up, weeks 73 to 91
RA screens for eligibility and development of delirium	X							
Daily delirium assessment: RASS and CAM-ICU-7^a^	_X_ ^a^							
DAST-10^a^	_X_ ^a^							
Informed consent	X							
Demographics		X						
Behavior checklist		_X_ ^b^			X		X	X
RBANS		_X_ ^b^			X		X	X
TMTs A and B		_X_ ^b^			X		X	X
SCWT		_X_ ^b^			X		X	X
IUTT		_X_ ^b^			X		X	X
SPPB		_X_ ^b^			X		X	X
SF-36		_X_ ^b^			X		X	X
GAD-7		_X_ ^b^			X		X	X
PHQ-9		_X_ ^b^			X		X	X
Delirium Experience Questionnaire		_X_ ^b^						
Lawton-Brody IADL		_X_ ^b^						
Katz ADL		_X_ ^b^						
QDRS		_X_ ^b^						
Randomization^c^		_X_ ^c^						
Medical history		X						
AE review and evaluation		X	X	X	X	X	X	X
Initial case review^d^			_X_ ^d^					
First virtual visit with CC^d^			_X_ ^d^					
Development of recovery care plan^d^			_X_ ^d^					
Second virtual visit with CC^d^			_X_ ^d^					
Interaction period^d^			_X_ ^d^	_X_ ^d^	_X_ ^d^	_X_ ^d^		

^a^RASS, CAM-ICU-7, and DAST-10 performed as needed during screening to confirm eligibility. RA may perform CAM-ICU-7 up to twice daily

^b^RA will obtain baseline measurements *ideally* within 48 h of anticipated hospital discharge *or* up to 4 weeks after discharge

^c^Randomization to occur *after* screening, consent, and completion of baseline assessments, *ideally* within 48 h of anticipated hospital discharge *or* up to 4 weeks

^d^EGS delirium recovery model only

This is a multicenter, prospective randomized controlled trial which will evaluate the efficacy of a collaborative care model, delivered via telehealth, in improving the cognitive, functional, and psychological recovery of older emergency general surgery delirium survivors. Our study sites span three states in the Midwest and include a safety net hospital serving many underprivileged and minority patients (Eskenazi Hospital), four community hospitals (Indiana University Health (IUH) North, IUH West, Meriter Hospital, and Swedish American Hospital), and three tertiary academic health centers (IUH Methodist, IUH University Hospital, and the University of Wisconsin Health University Hospital). Together, our team has assessed close to 8000 intensive care unit patients as well as older injured patients for eligibility and enrolled nearly 1000 patients into two NIH-funded trials. For this study, we plan to randomize 528 patients.

### Inclusion and exclusion criteria

Patients will be eligible for inclusion in this study if they are English-speaking, aged 65 years and older, admitted to one of our participating hospitals, and have undergone one of the following procedures in an emergent, urgent, or unplanned fashion: colectomy, small bowel resection, repair of peptic ulcer disease, lysis of adhesions, laparotomy, esophagectomy, liver resection, hepatopancreatobiliary surgery, gastrectomy, hernia repair, cystectomy, gynecological surgery, major vascular procedures, and major orthopedic (e.g., fractures) procedures. They will also need to be able to provide consent or have a legally authorized representative to provide consent, have access to a telephone or Internet-connected computer or smart device, be discharged to home or sub-acute rehabilitation, and have had at least one episode of delirium in the period prior to discharge from acute care.

Broadly speaking, the exclusion criteria will target patients in overall declining health, for whom it may be unethical to intervene or for whom there is no expectation of full recovery. These include a self-reported diagnosis of cancer with short life expectancy (< 6 months), current chemotherapy or radiation therapy confirmed in the electronic medical record (EMR), a history of Alzheimer’s disease and related dementias (ADRD) and other neurodegenerative disorders such as Parkinson’s disease or vascular dementia, incarcerated or unhoused status at the time of enrollment, acquired neurologic injury (stroke, traumatic brain injury, cerebral edema/swelling, anoxic brain injury, or any other acute/subacute neurologic deficit) as the admitting diagnosis or during the course of the hospital stay, a history of bipolar disorder or schizophrenia confirmed by EMR, current alcohol consumption > 5 drinks per day by self-report and/or confirmed by EMR, and history of drug abuse within the last 3 months.

### Ethics and informed consent

Both the University of Wisconsin and Indiana University Institutional Review Boards (IRB) approved this randomized controlled trial. This trial is registered on ClinicalTrials.gov (NCT05373017). Our team will approach all eligible participants prior to discharge for enrollment. We will obtain informed consent from the patient or a legally authorized representative by a trained research assistant (RA) or research coordinator. After the explanation of the study, all potential trial participants will be given a printed and/or electronic consent document and HIPAA release form. All personnel will be IRB-approved and trained on confidentiality, ethical research practices, and enrollment procedures. All participant data will be collected, shared, and maintained within IRB and HIPAA guidelines, and only approved study team members will have access to the collected data. The data will be stored in a secure Research Electronic Data Capture (REDCap) database on a password-protected University of Wisconsin server.

### Adverse events

Adverse events will reported to the co-principal investigators, statisticians, and the Data Safety Monitoring Board (DSMB) as well as the IRB, with appropriate action as deemed per policy. We will also formally document such occurrences. Re-hospitalizations, emergency department visits, and deaths will be reported via EMR notifications or from family members/caregivers at the time of outcome assessments, which are provided to the DSMB at regular meetings. Any other adverse events will be provided by reports from patients or their families/caregivers.

### Study design

This study is a multi-site, randomized controlled clinical trial. Due to the nature of the intervention, we will perform a two-arm (1:1), single-blinded study to evaluate the superiority of the proposed DANE collaborative care model over usual care. At or near the time of discharge, enrolled patients will be randomized to receive the DANE intervention using a computer-generated randomization scheme, stratified by recruitment site and whether the procedure was primarily vascular, due to the known delirium risk with that operation type. The comparator will be standard care, which will consist of postoperative care visits and calls as would be typical at the respective facility and under the guidance of the care team. Patients will then be followed for 18 months (Fig. 1).

**Fig. 1 Fig1:**
[figure not shown]
DANE Recovery Model study design

### Description of intervention

The Delirium and Neuropsychological Recovery among Emergency General Surgery Survivors (DANE) Recovery Model, our intervention, will occur across five phases corresponding to the guidelines established for conducting follow-up studies in injured patients [10]. Additionally, this study adheres to a conceptual model and classification scheme that organizes health outcomes into five levels [11]. During the acute stage (0–1 month after surgery), patients will undergo the initial case review and two initial virtual visits, and we will develop the recovery care plan. During the recovery stage (2–6 months after surgery) and maintenance stage (7–12 months after surgery), the patients will undergo the interaction phase of the DANE Recovery Model. Based on our prior work in a critical care recovery program targeting ICU survivors, we know that improvements in the recovery begin to manifest at 6 months, and we expect survivors of postoperative delirium to follow a similar trajectory [12].

At the initial case review, randomized patients, the care coordinator (CC) will introduce the DANE Recovery Model and determine the best mode of contact for future meetings. The time for the first visit will also be arranged, which marks the beginning of the recovery model.

After completing a pre-visit review, the CC will conduct the first virtual visit using a mobile visit technology to perform an initial assessment. The CC will also perform a social and community needs assessment, reconcile all prescribed and over-the-counter medications, and note all scheduled and recommended appointments with specialists, physical and occupational therapists, and other providers. The Healthy Aging Brain Care (HABC) Monitor will be used to evaluate and track cognitive, functional, and psychological symptoms of patient and caregiver stress and to trigger the use of specific treatment protocols [13].

The second virtual visit will include a detailed discussion of the individualized recovery care plan with the patient and caregivers, which will include the process of monitoring recovery progress, implementation of recovery protocols, distribution and explanation of educational materials, and connection to in-home and community resources as needed.

The 12-month interaction period with patients and/or informal caregivers will include virtual visits, phone calls, email, and mail. The minimum amount of contact during this period will be every 2 weeks. At the end of the interaction period, the CC will transition the care to the patient’s primary care physician. Activities during these interactions will include addressing any questions, collecting feedback, reviewing/reconciling medications and adherence, scheduled appointment reviews, HABC Monitor assessments, sleep monitoring, and facilitating access to any other resources in the community if needed.

Participants are free to withdraw from participation in the study at any time upon request. Those who do so will be informed that no new procedures will be performed after notice of study withdrawal. Information obtained up to that point will remain part of the study. The reason for withdrawal will also be recorded.

### Usual care

Patients randomized to usual care will also receive an initial review by the care coordinator prior at or near hospital discharge to confirm eligibility criteria, contact information, review discharge and rehabilitation plans, identify the primary care physician, and compose and send care transition information. Patients in the usual care group will receive no further interventions after this initial review. Concomitant care including prescription medications, over-the-counter medications, and supplements is permitted and will be tracked by the study team.

### Randomization and blinding

On or within 48 h of anticipated hospital discharge and after obtaining informed consent, the RA will obtain baseline measurements of physical function, depression, anxiety, quality of life, and cognitive ability. Subjects will then be randomized in a 1:1 manner via a computer-generated randomization scheme, stratified by recruitment site and surgery type (vascular or non-vascular surgery). All subjects will receive the interventions described under usual care. We will make every effort to blind the research staff performing the assessments to the intervention group. Intervention allocation will be coordinated centrally through the University of Wisconsin to minimize staff exposure to randomization assignments. Furthermore, the study staff will adhere to a strict study script during survey administration with patients and caregivers, and a standardized chart abstraction protocol with a data dictionary will be used. Due to the type of intervention, blinding of the patients is not possible. Physicians and other providers caring for the patient will be made aware of the study but not its objectives. Though collaborative care adverse event rates are low, blinded adverse event rates will be presented to the statistician and principal investigators throughout the trial. Decisions regarding unblinding will be made if there are elevated adverse event rates. The research team will be unblinded should any serious adverse events be deemed to be related to the intervention and the DSMB notified immediately.

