### Assessments and outcomes

The primary aims of this study are to evaluate the efficacy of the DANE Recovery Model to improve the cognitive recovery of older emergency surgery delirium survivors, as determined by the Repeatable Assessment of Neuropsychological Status (RBANS). Secondary aims include evaluation of physical and psychological recovery, as measured by the Short Physical Performance Battery, Medical Outcomes Study Short Form (SF-36), Patient Health Questionnare-9 (PHQ-9), and Generalized Anxiety Disorder Scale (GAD-7).

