### Data collection

Chart review will be used to abstract relevant covariables. Baseline assessments will occur at or as close (within 4 weeks) to hospital discharge as possible. After baseline assessments, outcomes will be collected at 6, 12, and 18 months. We will make every effort to retain patients during the 18-month study period and complete all follow-up instruments. We will attempt to do this in person. We will abstract data in a standardized fashion into a REDCap database. We will ensure data quality by independent abstraction and double data entry of 10% by the site PI or suitable designee. Any changes to the study protocol, including those related to the inclusion and exclusion criteria, will be communicated to key personnel, trial participants, program officers, and IRBs.

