### Description of study instruments

#### Repeatable Battery for the Assessment of Neuropsychological Status (RBANS) [14]

This is a commonly used battery for cognitive function. Originally developed as a screening instrument for older adults with suspected dementia, it is now used in a wider age range and a variety of neuropsychological problems. This instrument is comprised of twelve subtests that aggregate to a total and index score across five domains: immediate memory, visuospatial-constructional, language, attention, and delayed memory. Index scores are then converted to age-based standard scores (M = 100, SD = 15). The test is versatile with four equivalent forms to allow for serial assessment. It takes approximately 30 min to administer.

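### The unblinding rule for a related serious adverse event is neither limited to the affected participant nor closed to outcome assessors

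*Protocol article*

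**What the plan says.** Under Study design the trial is described as single-blind: "we will perform a two-arm (1:1), single-blinded study to evaluate the superiority of the proposed DANE collaborative care model over usual care". Under Randomization and blinding the article explains that the blind cannot be the patient's: "Due to the type of intervention, blinding of the patients is not possible". What is left is masking of the assessors, promised as a best effort: "We will make every effort to blind the research staff performing the assessments to the intervention group". Allocation is also handled centrally so that staff see few assignments, and surveys follow a fixed script.

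The same section then gives two unblinding provisions. For raised event rates a decision is to be taken: "Decisions regarding unblinding will be made if there are elevated adverse event rates". For a related serious event the consequence is automatic: "The research team will be unblinded should any serious adverse events be deemed to be related to the intervention and the DSMB notified immediately".

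The primary outcome is the RBANS, a battery given by staff ("It takes approximately 30 min to administer"). The secondary outcomes are the SPPB, a performance test, and the SF-36, PHQ-9 and GAD-7 questionnaires. Follow-up timing is given under Data collection: "After baseline assessments, outcomes will be collected at 6, 12, and 18 months".

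**The concern.** In an open-label trial with a tester-administered primary outcome, the tester's ignorance of allocation is the main protection against differential prompting, timing and scoring. A safety rule that can remove it should say whose allocation is disclosed and to whom. This one says neither. A site that followed the sentence as written could give assessors the allocations of participants who had nothing to do with the event. Visits before and after that date would then differ in quality, and lost blinding cannot be restored.

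The rule also has little visible safety purpose as far as assessors are concerned. Care coordinators already know whom they treat, and an event judged related to the intervention already implies that the participant received it. Those who must respond do not need outcome assessors to be told.

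**Working it through.** **Passages side by side (all under Randomization and blinding)**

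| Element | Assessor masking | Raised event rates | Related serious event |
|---|---|---|---|
| Trigger | none | elevated rates | any one event |
| Force | best effort | a decision is taken | automatic |
| Who | staff doing assessments | not stated | the research team |
| Whose allocation | all participants | not stated | not stated |

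The last column is the only automatic one. Nothing in it keeps assessors out or confines disclosure to one participant, so the first and last columns can collide.

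**How many assessments could be exposed**

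Inputs: 528 participants, 264 per group, 30% attrition and 185 per group after attrition (Statistical analysis); three follow-up visits (Data collection); accrual target of 15 per month, expected 24 per month (Recruitment and retention).

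- Scheduled follow-up assessments: 528 × 3 = 1,584. With 185 completers per group: 370 × 3 = 1,110.
- Narrow reading (one participant): at most 3 of 1,584, or 0.2%.
- Literal reading (trial-wide): let participant i (i = 0 to 527) enter at month i/15, with visits 6, 12 and 18 months later, and ignore attrition. At trigger month m, the share outstanding is 1 − (visits due by m)/1,584.
  - m = 12: 91 + 1 + 0 = 92 due; 1 − 92/1,584 = 94%.
  - m = 24: 271 + 181 + 91 = 543 due; 1 − 543/1,584 = 66%.
  - m = 36: 451 + 361 + 271 = 1,083 due; 1 − 1,083/1,584 = 32%.
  - At 24 per month the same shares are 91%, 45% and 6%.

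**How likely the trigger is**

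The article calls adverse event rates low but gives no figure, so the per-patient risk p of a related serious event is an assumption. The chance of at least one among 264 intervention patients is 1 − (1 − p)^264:

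| Assumed p | Chance of at least one |
|---|---|
| 0.05% | 12% |
| 0.1% | 23% |
| 0.25% | 48% |
| 0.5% | 73% |
| 1% | 93% |

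A low individual risk therefore does not by itself make the trial-level chance negligible. The section on the data safety monitoring board pulls the other way. Death, readmission, depressive and anxiety symptoms, agitation and falls are tracked as clinical outcomes and need not be reported as adverse events, which makes p smaller.

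**Size of bias**

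This cannot be derived from the document. As a yardstick only, an assumed assessor shift of 0.1 SD would be 0.1/0.2 = one half of the planned 6-month effect and 0.1/0.4 = one quarter of the planned 12- and 18-month effects.

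**The case against.** The strongest reply is that the sentence can be read narrowly. It is tied to one event and can mean disclosure for that case. The section uses different words for the team and for the staff who do assessments, and it never equates them. A reader might infer that the whole team is unblinded for the whole trial and that assessor blinding ends. The text does not say so; it leaves the scope open. This stands, and the point is therefore an unsafe, undefined rule and not a proven plan to unmask everyone.

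Three further inferences are tempting and also go too far:

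- That every outcome depends on assessor masking. The SF-36, PHQ-9 and GAD-7 are answered by patients who know their arm, so blinded staff and a fixed script protect them only in part.
- That unblinding for raised event rates is settled inside the study team. The article names no decision-maker. Blinded rates go to the statistician and principal investigators, and the DSMB also receives adverse event reports.
- That the trigger is likely. What qualifies must be serious, must fall outside the listed clinical outcomes if it is to be reported at all, and must be judged related to care coordination given by virtual visit, phone, email and mail.

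It can also be said that the article condenses a fuller protocol (version 7.0), which may define the scope. That would excuse silence. Here a rule is stated, in mandatory terms, next to a commitment that it can defeat. If the full protocol already limits it, the two texts need only be brought into line.

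**Conclusion.** The point holds as a badly worded rule. One related serious event is enough, the consequence is automatic, and nothing shields the assessors or other participants' allocations. The RBANS and SPPB have most to lose.

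The possible exposure runs from at most 3 assessments to roughly a third to nearly all of the 1,584 scheduled (32% to 94% for a trigger between months 36 and 12). The upper range assumes trial-wide disclosure that reaches assessors, uniform accrual at 15 per month and no attrition. The probability of the trigger is undocumented and probably low, and the resulting bias is not computable. No stated figure in the plan is wrong on this account. The reason to act is that the harm would be irreversible and the correction is nearly free, provided it is made before any such event.

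**What to change.** Rewrite the sentence so that a serious adverse event deemed related to the intervention leads to disclosure of that participant's allocation only, and only to the DSMB, its safety officer and those who must act on the event. Add that staff who perform outcome assessments remain blinded to all allocations until the end of follow-up. Keep the immediate DSMB notification as it is.

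Cost: a minor protocol amendment and slightly tighter handling of safety information at the sites. Sample size, alpha and staffing do not change, since the DSMB, the safety officer and central allocation are already in place.
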